## Abstract

**Background:**

The high prevalence of women that do not reach the recommended level of physical activity is worrisome. A sedentary lifestyle has negative consequences on health status and increases health care costs. The main objective of this project is to assess the cost-effectiveness of a primary care-based exercise intervention in perimenopausal women.

**Methods/Design:**

The present study is a Randomized Controlled Trial.

A total of 150 eligible women will be recruited and randomly assigned to either a 16-week exercise intervention (3 sessions/week), or to usual care (control) group.

The primary outcome measure is the incremental cost-effectiveness ratio. The secondary outcome measures are: i) socio-demographic and clinical information; ii) body composition; iii) dietary patterns; iv) glycaemic and lipid profile; v) physical fitness; vi) physical activity and sedentary behaviour; vii) sleep quality; viii) quality of life, mental health and positive health; ix) menopause symptoms. All outcomes will be assessed at baseline and post intervention. The data will be analysed on an intention-to-treat basis and per protocol. In addition, we will conduct a cost effectiveness analysis from a health system perspective.

**Discussion:**

The intervention designed is feasible and if it proves to be clinically and cost effective, it can be easily transferred to other similar contexts. Consequently, the findings of this project might help the Health Systems to identify strategies for primary prevention and health promotion as well as to reduce health care requirements and costs.

**Trial registration:**

ClinicalTrials.gov Identifier: NCT02358109. Date of registration: 05/02/2015

## Background

Physical inactivity is a pandemic and a leading risk factor for mortality [1]. Worldwide, 31.1 % of adults are physically inactive [2]. Inactivity rises with age, is higher in women than in men, and is increased in high-income countries [2]. In Spain, 50.2 % of adults are physically inactive (47.4 and 53.1 % in men and women, respectively) [2]. The elevated percentage of women who do not reach recommended level of physical activity is worrisome. A recent study in Spain [3] found that women aged from 41 to 50 years emerged as the groups with a greater likelihood of being sedentary in their leisure time. This physical inactivity-derived problem can be especially relevant during the perimenopausal period. Beyond the negative effects of physical inactivity [1], menopause increases cardiometabolic risk factors due to the significant decline in the estrogen levels [4, 5]. Moreover, menopause-related testosterone predominance appears to be implicated as a key hormonal change associated with the incidence of metabolic syndrome, independent of aging and other standard cardiovascular disease (CVD) risk factors [6]. Regular physical activity is associated with decreased risk of CVD and type 2 diabetes in middle aged women, independently of their menopause status [7]. Similarly, some studies observed that postmenopausal women with high physical activity levels had a more favourable CVD risk profile than their physically inactive peers [8, 9]. Additionally, higher physical activity is directly associated with better health-related quality of life [10, 11]. Indeed, exercise interventions can improve sleep quality [12] and depression [13] in middle adult women. However, the role of physical activity in clinical practice remains undervalued despite increasing evidence supporting its protective effects and the economic burden associated with a sedentary lifestyle [1].

National Health expenditures in Spain have increased from 7.2 % of the gross domestic product (GDP) in 2001 to 9.3 % in 2011 [14]. The pharmacological treatment costs are specially increasing in European countries [14]. In Spain, pharmacological costs represent 1.6 % of the GDP, and 17.4 % of the National Health Expenditures [14]. Previous studies have shown that regular physical activity reduces health care requirements and thereby leads to significant savings in health-care costs [15, 16].

In 2005, the Spanish Ministry for Health and Consumption designed the Strategy for Nutrition, Physical Activity and Prevention of Obesity (NAOS) with the aim of promoting a healthy lifestyle among the general population. Additionally, in May 2009 the Spanish National Sports Council launched the Integral Plan on Physical Activity and Sport (A + D Plan). This plan included a specific program focused on women, with the objective of increasing their physical activity levels. In this context, we designed the Fitness League Against MENopause COst (FLAMENCO) project, a randomized controlled trial to investigate the cost-effectiveness of an exercise intervention in primary care settings in middle aged women.

The primary aim of the FLAMENCO project is to assess the cost-effectiveness of a primary care-based exercise intervention program (16 weeks) in perimenopausal women. In addition, we will address the following specific objectives: i) to determine the associations between physical activity, sedentary behaviour and physical fitness with CVD biomarkers, body composition, dietary patterns, glycaemic and lipid profile, sleep quality, quality of life, mental health, positive health and menopause symptoms; and ii) to study the associations between the above mentioned variables with pharmacological and health service costs.

The purpose of this methodological article is to describe the study design, procedures and methods that will be used in the “FLAMENCO project”.

## Methods/Design

The present study is a Randomized Controlled Trial (RCT) (registration number: NCT02358109). The study protocol has been reviewed and approved by the Ethics Committee for Research Involving Human Subjects at the University of Granada. The participants will have to provide a written informed consent before taking part in the study, which will be conducted in accordance with the CONSORT (Consolidated Standards of Reporting Trials) statement.

### Participants and recruitment process

Women will be recruited through primary care centres from Granada (Southern Spain). Medical staff will recruit possible candidates for participation during consultations at the primary care centres. Furthermore, press releases will be published in local newspaper and on social media (radio, internet, etc.). Moreover, information leaflets will be distributed in primary care centres and informative meetings with potential participants will be carried out.

A screening of all candidates will be performed. The inclusion and exclusion criteria are shown in Table 1. The organizational and participants flow is presented in Fig. 1.

**Table 1 Tab1:** Inclusion and exclusion criteria in the FLAMENCO project

Inclusion criteria
- Age: 45–60 years old.
- Not to have severe somatic or psychiatric disorders, or diseases that prevent physical exercise (Answer “no” to all questions on the PAR-Q).
- Not to be engaged in regular physical activity >20 min on >3 days/week in the last three months.
- To be able to ambulate without assistance.
- To be able to communicate.
- Informed consent: To be capable and willing to provide informed consent.
Exclusion criteria
- Acute or terminal illness.
- Myocardial infarction in the past 3 months.
- Unstable cardiovascular disease or other medical condition.
- Upper or lower extremity fracture in the past 3 months.
- Unwillingness to either complete the study requirements or to be randomised into control or intervention group.
- Presence of neuromuscular disease or drugs affecting neuromuscular function.

PAR-Q: Physical Activity Readiness Questionnaire

**Fig. 1 Fig1:**
[figure not shown]
The organizational and participants flow

### Sample size

The number of participants to be included in the study was calculated on the basis of the change in quality of life as assessed with the *EuroQol 5D (*EQ-5D-5 L). To the best of our knowledge, there is no available data regarding group differences in changes in quality of life following any type of intervention in middle aged women. Therefore, we assumed a difference of 0.07 units as clinically meaningful based on previous observations from our group (unpublished observations). Therefore, a total of 124 participants (62 per group) is needed to detect a mean group difference of 0.07 and a standard deviation of 0.12 in the total EQ-5D score with a power of 90 % and α of 0.05. However, we will attempt to exceed this sample size to allow for withdrawals. Assuming a maximum lost-to-follow up of 20 %, a minimum of 75 participants per group will be recruited (*n* = 150).

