### Randomization and blinding

After baseline assessments, all participants will be randomized to either exercise intervention or control (non-exercise) group. A computer generated simple randomization sequence will be created before participants will be enrolled, to allocate participants to either the exercise intervention or control group (1:1). The randomization sequence will be prepared by a member of the research team with no clinical involvement in the trial. The allocation will be concealed in a password protected computer file. Whereas the participants will be aware of their group allocation, outcome assessors and data analysts will be blinded to the allocation.

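### The recruitment target of 75 per group does not cover the stated 20 % loss: it leaves 60 women per group, below the 62 the plan says it needs

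*Protocol article*

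**What the plan says.** The protocol article, section Sample size, bases the size on the change in EQ-5D-5L and states that "a total of 124 participants (62 per group) is needed to detect a mean group difference of 0.07", with "a standard deviation of 0.12 in the total EQ-5D score" and "with a power of 90 % and α of 0.05". It then says that recruitment should go beyond this number to allow for withdrawals. Taking 20 % as the maximum loss to follow-up, it concludes that "a minimum of 75 participants per group will be recruited", 150 in total. No inflation formula is given.

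The Methods/Design paragraph of the Abstract repeats the total without the word minimum: "A total of 150 eligible women will be recruited and randomly assigned". No other section revises either number.

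**The concern.** The section pairs a worst-case loss with a smallest recruitment figure. Read together, they promise that if no more than 20 % of the women are lost, the number required for 90 % power will still be there. That promise can be checked by one multiplication, and it fails.

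Readers use the sample size statement to judge whether a trial still met its requirement after the attrition it observed. As written, losses above 17.3 % and up to 20 % would put the trial inside its declared allowance and yet below its declared requirement. What is at stake is the accuracy of that statement and about one point of power at the limit of the allowance, not the validity of the trial.

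**Working it through.** **Inputs** (section Sample size, unless noted): difference 0.07; standard deviation 0.12; α 0.05; power 90 %; 62 per group required; maximum loss 20 %; 75 per group to be recruited; 1:1 allocation (section Randomization and blinding). The article does not say whether α is one- or two-sided. I take two-sided, because that reproduces the stated 62; a one-sided test would need only 51 per group.

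**1. The plan's base figure.** With the normal approximation for two means,

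n per group = 2 × (1.960 + 1.2816)² × (0.12/0.07)² = 61.8, rounded up to 62.

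This matches the plan, so the inputs are not in dispute. A t-test calculation gives 62.7, so 63.

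**2. The allowance for loss.** If a fraction d of those recruited is lost, N × (1 − d) remain. To keep n, recruit N = n/(1 − d):

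- 62/(1 − 0.20) = 77.5, so 78 per group, 156 in total (155 if 124/0.80 is taken on the total).
- 62 × (1 + 0.20) = 74.4, so 75 per group, 150 in total.

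Only the second calculation gives the printed target. Rounding does not explain the gap, since 77.5 rounds to 77 or 78.

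**3. What 75 per group delivers.**

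- At 20 % loss: 75 × 0.80 = 60 per group, 120 in total. This is 2 per group short of 62 and 4 short of 124.
- Largest loss that still leaves 62: 1 − 62/75 = 13/75 = 17.3 %.

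**4. Effect on power.** For an unadjusted two-group comparison with standardised difference 0.07/0.12 = 0.583, the normal approximation is power = Φ(0.583 × √(n/2) − 1.960):

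| Women per group | Normal approximation | t test |
|---|---|---|
| 60 (75 recruited, 20 % lost) | 89.2 % | 88.7 % |
| 62 (stated requirement) | 90.1 % | 89.7 % |
| 75 (no loss) | 94.7 % | 94.4 % |

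Within either method, going from 62 to 60 costs about 1 percentage point. The t-test figure of 88.7 % should not be set against the nominal 90 % as the cost of this error, because part of that gap comes from the plan's use of the normal approximation.

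**The case against.** The arithmetic itself is hard to contest. The case on the other side is that it hardly matters, and it has five parts.

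- **75 is a minimum and 20 % a maximum.** This does not help. That pairing is exactly the case the sentence is meant to guarantee, and the Abstract gives 150 as a plain total.
- **The analysis keeps everyone.** The section Statistical analysis plans intention-to-treat with multiple imputation, and EQ-5D-5L is also collected at 8 weeks, so a woman lost later can still contribute something. But imputation does not recreate the outcome information that is lost, and the same section plans a sensitivity analysis without imputation. The authors themselves treat 62 as a number to be protected against withdrawals.
- **Covariate adjustment may recover the loss.** This has substance. The planned model adjusts for baseline. If 0.12 is the standard deviation of the score and the baseline–outcome correlation is 0.2, 0.3 or 0.5 (assumed values; the article gives none), the residual standard deviation is 0.12 × √(1 − r²), and t-test power with 60 per group is about 89.9 %, 91.3 % or 95.5 %. So 89 % need not be the power of the planned analysis. Still, the sample size section claims no such gain, and its 62 is reproduced without one.
- **Chance imbalance is larger.** Under simple 1:1 randomisation of 150 women, the size of an arm has a standard deviation of √(150 × 0.25) = 6.1, which exceeds the shortfall of 3. This is true and helps to show how small the effect is, but it does not make the stated figure right.
- **The cause is inferred.** This stands: the article does not say that the 20 % was applied by multiplication. The shortfall does not depend on it, because 60 is below 62 however 75 was reached.

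**Conclusion.** The concern holds. The stated target does not deliver the stated requirement at the stated loss: 75 per group with 20 % lost leaves 60, not 62. The target consistent with the plan's own inputs is 78 per group, 3 more per group than planned.

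The consequence is minor. Power at the limit of the allowance is about 89 % instead of 90 %, and up to 17.3 % loss the allowance does what it was written to do. These power figures assume a two-sided α of 0.05, an unadjusted comparison of women with outcome data, and equal loss in both groups. Baseline adjustment could make up the difference, but only with a correlation that the article does not state. The sentence is wrong as written and should be corrected; the design does not have to change.

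**What to change.** Correct the last sentence of the Sample size section. The simplest version keeps 150 women and states what that number supports: 75 per group retains at least 62 with outcome data as long as loss does not exceed about 17 %, and at 20 % loss the power is about 89 %. This requires no additional participants and no change to the design; its only cost is a slightly less favourable statement of the allowance or the power.

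The alternative is to keep the 20 % allowance and state 78 per group (156 in total), in the Abstract as well. That means six more women. It would be consistent, but it is not needed to resolve the point.

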### Randomization and blinding

After baseline assessments, all participants will be randomized to either exercise intervention or control (non-exercise) group. A computer generated simple randomization sequence will be created before participants will be enrolled, to allocate participants to either the exercise intervention or control group (1:1). The randomization sequence will be prepared by a member of the research team with no clinical involvement in the trial. The allocation will be concealed in a password protected computer file. Whereas the participants will be aware of their group allocation, outcome assessors and data analysts will be blinded to the allocation.

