### Interventions

The participants randomly assigned to the usual care (control) group will receive general advices from primary care centre medical staff about the positive effects of physical activity. The researchers will give 4 conferences (1 per month) explaining the benefits of exercise for longevity, prevention and treatment of diseases, the benefits of the Mediterranean diet, nutritional education, ergonomic advises, exercise to perform at home (e.g. stretching, strength training) and strategies to increase their daily physical activity levels.

The exercise intervention will be performed in four groups so that each group will comprise 15–20 participants. The groups will train 3 days/week (60 min per session) for a 16-week period at the primary care centre of Granada. The exercise intervention will meet the training standards of the American College of Sports Medicine [17] for adults. The exercise sessions will be designed, carefully supervised, guided and instructed by qualified exercise professionals.

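### Simple randomisation of 150 women cannot guarantee, and will very probably miss, the stated minimum of 75 per group, and it may overfill the four planned exercise classes

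*Protocol article*

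**What the plan says.** Three statements in the protocol article bear on this point.

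- **Randomization and blinding:** "A computer generated simple randomization sequence will be created before participants will be enrolled". The ratio is 1:1, and no blocks or strata are mentioned. A team member without clinical involvement prepares the sequence, and it is held in a password-protected file. Participants know their group; outcome assessors and analysts do not.
- **Sample size:** "a total of 124 participants (62 per group) is needed", and after an allowance for 20 % loss "a minimum of 75 participants per group will be recruited", with n = 150. The Abstract repeats the total: "A total of 150 eligible women will be recruited and randomly assigned".
- **Interventions:** "The exercise intervention will be performed in four groups so that each group will comprise 15–20 participants".

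**The concern.** With 150 women in total, a minimum of 75 in each group can be met only by an exact 75:75 split. Four classes of 15 to 20 imply an exercise arm of 60 to 80. Under simple randomisation the arm sizes are random, so the method does not control either figure. The article does not say how the per-group number would be reached, or what happens if more than 80 women are allocated to exercise.

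What is at stake is whether the trial can be run as described. The per-group size reported at the end would probably differ from the one stated, and the classes might have to be enlarged or increased in number after allocation.

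**Working it through.** **1. The plan's own sample size.** Inputs from the Sample size section: difference 0.07, SD 0.12, power 90 %, α 0.05 (two-sided assumed; the article does not say, but this reproduces its figure).

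n per group = 2 × [0.12 × (1.960 + 1.282) / 0.07]² = 61.8, so 62 per group and 124 in total. This agrees with the article.

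The step to 75 reproduces as 62 × 1.2 = 74.4, rounded up. Dividing by the expected retention would give 62 / 0.8 = 77.5, so 78. That is a separate matter, taken up only under the fix.

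**2. Arm size at N = 150.** Let X be the number allocated to exercise. Under simple 1:1 randomisation X ~ Binomial(150, 0.5), with mean 75 and SD √150 / 2 = 6.1.

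| Event | Probability |
|---|---|
| Exactly 75:75 | 6.5 % |
| One arm below 75 | 93.5 % |
| Smaller arm 70 or fewer | 46 % |
| Smaller arm below 62, before any dropout | 2.7 % |
| Exercise arm above 80 | 18.5 % |
| Exercise arm below 60 | 0.6 % |
| Exercise arm within 60 to 80 | 81.0 % |

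The 2.5 % and 97.5 % quantiles of X are 63 and 87.

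**3. Does recruiting past 150 rescue the plan?** For a total of N, the chance that both arms reach 75 is P(75 ≤ X ≤ N − 75). The chance of meeting both the minimum and the class limit is P(75 ≤ X ≤ min(80, N − 75)).

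| N | Both arms ≥ 75 | Both arms ≥ 75 and exercise arm ≤ 80 |
|---|---|---|
| 150 | 6.5 % | 6.5 % |
| 155 | 37.0 % | 37.0 % |
| 160 | 61.5 % | 33.9 % |
| 175 | 95.1 % | 12.0 % |

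The joint chance peaks at 37 % (N = 155). At N = 175, where the minimum is nearly assured, the exercise arm exceeds 80 with probability 85.5 %.

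**4. Cost in power.** Normal approximation, difference 0.07, SD 0.12, two-sided 5 %:

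| Split | No loss | After 20 % loss |
|---|---|---|
| 75:75 | 94.7 % | 89.2 % |
| 63:87 | 94.1 % | 88.4 % |
| Average over simple randomisation | 94.5 % | 89.0 % |

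At the edge of the 95 % range the loss is 0.6 to 0.8 points. On average it is 0.1 to 0.2 points.

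**5. The proposed blocks.** Fifteen blocks of 4 and fifteen of 6 contain 15 × 4 + 15 × 6 = 150 women, with 15 × 2 + 15 × 3 = 75 in each arm. That gives 75 / 4 = 18.75, about 19 women per class. Blocks of 4 and 6 drawn freely and cut off at 150 would still end 74:76 in about 22 % of runs, so the lengths should be made to sum to the total.

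**The case against.** Simple randomisation is a valid, unbiased method. The 75 is a recruitment target built from 62 plus a dropout allowance, and the text calls it a minimum, so recruiting more than 150 is not excluded. The 93.5 % counts a 74:76 split as a failure, which harms nobody. The article gives a planned class size, not a room limit: averaging more than 21 per class needs over 84 women (6.0 %), and more than 22 needs over 88 (1.4 %). The participant-flow figure is not shown, and the full protocol may describe recruitment in waves or a list with fixed totals.

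Much of this stands, and it sets the size of the point. What does not stand is the appeal to recruiting beyond 150, because that makes the class figure harder to meet (step 3).

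Four stronger readings are tempting, and the document does not support them:

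- **That simple randomisation cannot deliver 75 per group.** It can, in 6.5 % of runs at 150. It cannot guarantee it.
- **That the comparison would be biased or materially underpowered.** Allocation is unbiased and the power loss is under one point across the 95 % range.
- **That blocking would remove extra variance in the cost and EQ-5D comparisons.** Unstratified blocks balance numbers, not prognostic covariates, so the only gain in precision is the small one in step 4.
- **That blocking costs nothing.** Participants know their group, so late allocations within a block become somewhat easier to guess.

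**Conclusion.** The point holds as a minor defect of feasibility and consistency. The stated allocation method does not control the stated group size or class size, and no total number recruited makes both likely to hold together. The result rests on reading simple randomisation as independent 1:1 assignment of each woman, and on taking four classes of 15 to 20 as a planned range of 60 to 80. If the full protocol uses a list with fixed totals, only the wording of the article needs correcting.

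**What to change.** In the randomisation section, replace simple randomisation with computer-generated 1:1 permuted blocks in random order, with lengths that sum to 150, for example fifteen blocks of 4 and fifteen of 6. Keep the independent preparer and the concealed file as written, and add that block sizes are withheld from recruiting staff.

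If the total is revised, choose block lengths that sum to the new total. At 78 per group (156 in all) the exercise arm would still fit four classes of up to 20.

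The change costs a sentence or two in the protocol and a different setting in the sequence generator, with no extra participants or staff. The one drawback is slight predictability of late-in-block allocations, which varied, undisclosed block sizes and the planned concealment limit but do not remove.
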